## Methods/design

### Study design

To evaluate the effect of tailoring the pDDI knowledge base to the ICU setting on pDDI prevention we will implement a trial with a stepped-wedge design. A stepped-wedge trial is a type of cluster trial in which an intervention is rolled-out sequentially to the clusters over a number of periods that are called ‘steps’ [21]. By the end of the trial period, all clusters will have received the intervention. The order in which the clusters receive the intervention is randomized [22]. Data analysis to determine the overall effectiveness of the intervention subsequently involves comparison of the data points in the control section of the wedge with those in the intervention section [21].

We prefer a stepped-wedge design over a randomized controlled trial because withholding CDSS from those already using it is not considered ethical in our study. Withholding decision support in an environment where physicians are used to receive support to prevent pDDIs could have a negative effect on patient safety. Furthermore, methodologically speaking the stepped-wedge design is comparable to a parallel cluster RCT. Also, when the clusters are large, as is the case in our study, a stepped-wedge design is more powerful than a parallel design [23].

The order in which the ICUs will receive the intervention will be randomized, because randomization helps reduce the risk of bias and thereby increase the internal validity of the study [24]. An independent researcher who is not involved in further conduct of this study will perform the computerized randomization. As all the prescribing physicians in the participating ICUs and the investigators will be aware of the ‘step’ from control to intervention status, blinding is not feasible. Further details on the implementation of the stepped-wedge design in this study can be found in the paragraph ‘Stepped-wedge design implementation’.

This protocol is reported in accordance with the SPIRIT 2013 guideline for content of clinical trial protocols [25]. The results of this study will be reported in accordance with the CONSORT statement [26].

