### Stepped-wedge design implementation

In our study, each ICU represents one cluster and the MIM+ is rolled-out over nine steps of one month each (see Fig. 3). At each step, one cluster will start with the MIM+. Maximum power for a given number of clusters is achieved when each cluster has its own step [22]. The total duration of the trial is ten months. Whenever an ICU starts with the MIM+, the first month will be considered a pilot month, in which small, local changes to the MiM+ will be allowed. For example, an ICU could argue for the inclusion of an alert for an extra pDDI that was not included in the MiM+ or to discard a pDDI alert from the MiM+. This will be allowed, because the type of patients and medications can differ between ICUs and this could lead to different needs for pDDI alerts. We hypothesize that such local limited tweaking will rarely happen but can positively influence system acceptance [30].

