### Sample size

To calculate power of our stepped-wedge trial, the statistical software PASS 15.0.4 (NCSS LLC., Kaysville, UT) was used. The calculation considers the following factors: the number of steps, the size of the steps, the number of clusters per step, the number of medication administrations per cluster per step, the anticipated improvement of the intervention, the estimated event rate, and the estimated intra-cluster correlation (ICC).

The anticipated improvement was defined as the overall difference in the number of clinically relevant pDDIs per 1000 medication administrations before and after the MiM+ implementation. We estimate an average relative reduction of 20% in all participating ICUs. According to a systematic review assessing effects of IT-based interventions on outcomes related to DDIs, relative reductions ranging from 15 to 29% have been reported [9].

Based on preliminary analysis of medication data extracted from 5 out of the 9 participating ICUs and one ICU that does not participate in the MiM+ component of the intervention, the number of clinically relevant pDDIs per 1000 medication administrations was estimated to be 42.0 (event rate). With a relative reduction of 20%, the event rate after the intervention is therefore estimated to be 33.6. As an indicator of face validity, a senior intensivist who is involved in the study, considered that a 20% relative reduction from 42.0 is clinically relevant. With a sample of 9 clusters in a stepped-wedge cluster-randomized design with 10 time periods, 9 steps, and one cluster switching from control to intervention at each step and an average number of 6000 medication administrations per cluster, with an average of 600 medication administrations per cluster per time period, calculations show 83% power to detect a relative reduction of 20%, considering an estimated intra-cluster correlation of 0.12. The calculations are based on the Poisson distribution, the test statistic used is the two-sided Wald Z-Test and the significance level of the test is 0.05.

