### Statistical analysis

Depending on the distribution of variables, descriptive statistics will be presented as mean and standard deviation, median and IQRs, or percentage as appropriate. Continuous variables will be compared using the t-test or Mann-Whitney test. Categorical variables will be compared with a Chi squared test or Fisher’s exact test. To assess the effect of tailoring pDDI alerts to the ICU setting on the number of pDDIs per 1000 medication administrations we will analyse data from the stepped-wedge trial, adjusting for data clustering and for temporal trends if necessary. A generalized linear model will be fitted with correction for clustering via generalized estimating equations. To adjust for possible confounding patient characteristics (age and disease severity) and other variables (such as the previous use of MiM prior to MiM+) will be considered for addition in the model as covariates. We anticipate that most DDIs will occur around the third day of admission, because by that time chronic home medication often is restarted in the ICU while medication typically prescribed in the ICU is still prescribed [32].

All analyses will be performed according to the intention-to-treat principle. For hypothesis testing a probability level of less than 0.05 will be considered statistically significant. All statistical tests will be two-sided. The R statistical software environment will be used for the analyses.

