Lastly, consensus methods such as our Delphi procedure contain certain methodological issues such as bias in the selection of participants, and subjectivity in the judgements of expert panel members. To ensure experts involved are representative for the Dutch ICU care, we will not only invite experienced intensivist and hospital pharmacists from the participating hospitals but also from Dutch hospitals not participating in the trial. By using a scoring instrument and live panel discussion, we aim to limit subjectivity in judgments about clinical relevance of pDDIs.

As with cluster randomized trials in general, stepped-wedge designs require larger sample sizes because patients may be similar within one cluster. Even though randomization improves the balance of important characteristics across study arms, with a small number of clusters as in our study, such a balance cannot be ensured [22]. A second methodological limitation is the potential for confounding by temporal trends. Comparisons of outcomes between earlier and later periods may be influenced by background changes that affect the outcome of interest, irrespective of the intervention [22]. We believe that given the relatively short study period of 10 months this risk is limited.

Although in this study, for practical reasons, we use specific CDSS software (MiM+), the knowledge gained about which pDDIs are clinically relevant to the ICU can be used in any other type of CDSS. Therefore, if successful, implementing our set of clinically relevant pDDIs should be beneficial in other ICUs, also outside the Netherlands, as frequently occurring pDDIs in the ICU setting seem comparable between countries [34]. Our results may also encourage caregivers from other settings, and developers of CDSSs, to establish a pDDI knowledge base for a specific setting of patient group, for example for pediatric or oncology care.

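### Calendar time is adjusted for only conditionally, so a background trend could be reported as a MiM+ effect or could hide one

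*Protocol article*

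**What the plan says.** In the Statistical analysis section, the analysis of the stepped-wedge data is described as "adjusting for data clustering and for temporal trends if necessary". The model is given in one sentence: "A generalized linear model will be fitted with correction for clustering via generalized estimating equations". No period term is named in it. Age and disease severity are named as possible covariates, and "other variables (such as the previous use of MiM prior to MiM+) will be considered for addition in the model as covariates"; calendar time is not in that list.

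The Discussion names confounding by temporal trends as a limitation and then sets it aside: "We believe that given the relatively short study period of 10 months this risk is limited".

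The layout is fixed. Under Stepped-wedge design implementation, "the MIM+ is rolled-out over nine steps of one month each", with one ICU starting at each step. The Sample size section restates it as "9 clusters in a stepped-wedge cluster-randomized design with 10 time periods, 9 steps, and one cluster switching from control to intervention at each step".

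**The concern.** Each ICU moves once, from control to MiM+, and never back. Within an ICU every MiM+ month is later than every control month, so a within-ICU comparison that ignores the calendar attributes any background change to MiM+. What separates the two is the randomised, staggered start, and that information is used only if the model contains a period term. In a stepped wedge the term is part of how the effect is identified. It is not an optional refinement.

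The plan makes the term conditional and does not say on what. If the decision is taken after the data are seen, by a test or by judgement, it is taken by an unblinded team and affects the primary result. A falling trend would exaggerate the benefit; a rising one would conceal it.

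**Working it through.** **1. The plan's own power figure.** Inputs from the Sample size section: I = 9 clusters, T = 10 periods, "with an average of 600 medication administrations per cluster per time period", rates 42.0 and 33.6 per 1000, ICC 0.12, two-sided 0.05, Wald z, Poisson. The article does not print its formula. I used the Hussey-Hughes variance with fixed period effects and, as an assumption, the mean rate 0.0378 for the variance:

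Var = I·s²·(s² + T·τ²) / [(I·U − W)·s² + (U² + I·T·U − T·W − I·V)·τ²]

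- U = 1 + … + 9 = 45 intervention cluster-months; W = V = 1² + … + 9² = 285
- s² = 0.0378/600 = 0.000063; τ² = (0.12/0.88) × 0.0378 = 0.0051545
- numerator: 9 × 0.000063 × 0.051608 = 0.00002926
- denominator: 120 × 0.000063 + 660 × 0.0051545 = 3.4096
- SE = √(0.00002926/3.4096) = 0.00293
- power = Φ(0.0084/0.00293 − 1.96) = Φ(0.91) = 81.8%

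This is close to the stated 83%. The result is 77.6% if the control rate sets the variance and 86.0% if the intervention rate does. With no time term the SE falls to 0.00195 and power becomes Φ(2.34) = 99.0%, which is far from 83%.

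**2. The time gap.** For an ICU with k control months (k = 1 to 9), the mean control month is (k + 1)/2 and the mean MiM+ month is (k + 1 + 10)/2. The difference is 10/2 = 5.0 months for every k. Pooling all cluster-months, it is 3.67 months. Both figures count the pilot month as a MiM+ month. Leaving it out gives (k + 2 + 10)/2 − (k + 1)/2 = 5.5 months in the eight ICUs that still have MiM+ months.

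**3. Apparent effect with no true effect and no time term.** The monthly decline is an assumption. The apparent rate ratio is (1 − decline) to the power of the gap.

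| Decline per month | Within-ICU weighting (gap 5.0) | Independence working correlation (gap 3.67) |
|---|---|---|
| 1% | 0.99^5 = 0.951, 4.9% reduction | 3.6% reduction |
| 2% | 0.98^5 = 0.904, 9.6% reduction | 7.1% reduction |
| 3% | 0.97^5 = 0.859, 14.1% reduction | 10.6% reduction |

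A decline of about 4.4% per month would produce the whole 20% target by itself (0.8^(1/5) = 0.956).

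**4. Would a trend test protect the result?** With 600 × 0.042 = 25.2 expected events per ICU-month, the SE of a monthly linear trend, fitted alongside MiM+, is 0.0110 on the log scale. A 1% decline is then 0.01005/0.0110 = 0.92 SE from zero, detected about 15% of the time. A 2% decline is 1.84 SE, detected about 45% of the time.

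Simulation of 2,000 trials per row, with Poisson counts, ICU fixed effects, an assumed between-ICU log-SD of 0.3 and no MiM+ effect:

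| Decline per month | Type I error, no time | Time kept only if trend test p < 0.05 | Month always in | Trend test keeps time |
|---|---|---|---|---|
| 0 | 5.4% | 7.2% | 5.5% | 5.3% |
| 1% | 18.2% | 17.6% | 4.3% | 14.5% |
| 2% | 50.1% | 30.7% | 5.2% | 42.3% |

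**5. The planned GEE.** The table above is for a Poisson model with ICU fixed effects, which is not the planned method. Simulating GEE with uncorrected robust standard errors under the same kind of assumptions gave 26% (1% decline) and 62% (2% decline) without time, and 12-15% with categorical month. With a small-sample correction and month in the model it was 5-7%.

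**The case against.** The best defence is that the plan foresees the adjustment, names temporal confounding openly, and appears to have been sized for a period-adjusted model. The form of a time term is also ordinarily left to an analysis plan that is not shown here. Much of that stands. The form of the term is not the issue; the issue is that the article itself makes the term conditional and defends this by trial length.

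Four stronger readings are tempting, and the documents do not support them.

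- A reader might infer that MiM+ and time cannot be separated. Within one ICU they cannot; across nine ICUs with a randomised staggered start they can. The design is sound.
- A reader might infer that a trend will be reported as a MiM+ effect. That follows only if time is left out, and the plan allows for including it.
- The Study design section speaks of "comparison of the data points in the control section of the wedge with those in the intervention section". That is a general description of stepped-wedge trials. It does not specify this trial's model or exclude period terms.
- A reader might infer that a drift is likely. The documents give no estimate and do not mention seasonality. The feedback reports precede MiM+ but are undated in the text. If they are timed to each ICU's own start, calendar-month effects would not remove their influence.

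It is also fair to object that a period term alone does not restore 5% under GEE with nine clusters. That is correct, and the fix below includes it.

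**Conclusion.** The concern holds for the conditional adjustment. The 5.0-month gap follows from the layout alone, and the short-trial argument does not answer it, because the 10-month layout is what creates the gap. The apparent effects of about 5-10% (about 4-7% under independence) rest on assumed declines of 1-2% per month, equivalent to 8.6-16.6% over the nine monthly intervals. A smaller drift gives a proportionately smaller bias, and no drift gives none.

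The type I error figures rest in addition on Poisson variation, 600 administrations per cell and the assumed between-ICU spread. Overdispersion would lower the false-positive rate, and larger cells would raise it; neither changes the bias. An independence working correlation would also give less inflation, because its estimate is less biased and less precise.

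The match between 83% and 81.8% shows that the stated power is consistent with period adjustment. It does not prove which formula the software used.

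**What to change.** In the Statistical analysis section, delete the condition at the end of "adjusting for data clustering and for temporal trends if necessary". State that the primary model always contains calendar period in a prespecified form (month as a categorical effect, or a prespecified linear term), together with the MiM+ indicator and ICU clustering, whatever any trend test shows. If GEE is kept, name a small-sample correction for the standard errors. Categorical month plus intercept and MiM+ indicator is 11 mean parameters on nine clusters, so the correction matters most there. Remove the Discussion sentence claiming that the study length limits the risk.

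The cost is a few sentences. On the log scale the SE rises from 0.049 without time to 0.074 with it, but the stated power is consistent with a calculation that already carries this. The small-sample correction is a separate matter: it may cost some precision that a Wald z calculation does not show, and I have not quantified that.

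### The primary GEE analysis rests on nine ICUs at nominal 0.05 with no stated small-sample safeguard; the usual sandwich z test would exceed 5% type I error

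*Protocol article*

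**What the plan says.** All references are to the protocol article.

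- Statistical analysis, primary model: "A generalized linear model will be fitted with correction for clustering via generalized estimating equations". Time enters conditionally: "adjusting for data clustering and for temporal trends if necessary".
- Statistical analysis, decision rule: "For hypothesis testing a probability level of less than 0.05 will be considered statistically significant", and "All statistical tests will be two-sided".
- Sample size, layout: "With a sample of 9 clusters in a stepped-wedge cluster-randomized design with 10 time periods, 9 steps, and one cluster switching". For the power calculation, "the test statistic used is the two-sided Wald Z-Test and the significance level of the test is 0.05".
- Discussion, on few clusters: "with a small number of clusters as in our study, such a balance cannot be ensured". This concerns the balance of characteristics between conditions, not the validity of the test.

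The article does not name the variance estimator, the working correlation, the reference distribution of the primary test, or any small-sample correction or permutation test.

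**The concern.** The sandwich variance used by default with GEE is consistent as the number of clusters grows. With few clusters it is biased downward, because the residuals it is built from have been shrunk by the fit. A normal reference also ignores the variability of the variance estimate itself. Both errors make the test reject too often. Nine is a very small number of clusters, and with one term per month plus treatment the mean model would have 11 parameters.

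What is at stake is the primary conclusion. The p-value would overstate the evidence and the 95% interval would be too narrow. The published power is affected too, because it assumes a normal-reference test that nine clusters do not support.

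**Working it through.** **Step 1. Reproduce the stated power (83%).**

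Inputs from the Sample size section: I = 9 ICUs, T = 10 periods, one ICU switching per step, 600 administrations per ICU-period, rates 0.0420 and 0.0336 (difference 0.0084), ICC 0.12, two-sided Wald Z at 0.05.

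Hussey-Hughes variance:

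Var = Iσ²(σ² + Tτ²) / [(IU − W)σ² + (U² + ITU − TW − IV)τ²]

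- U = 45 and W = V = 285, so IU − W = 405 − 285 = 120.
- U² + ITU − TW − IV = 2025 + 4050 − 2850 − 2565 = 660.
- Average Poisson variance = 0.0378, so σ² = 0.0378/600 = 0.000063 and τ² = (0.12/0.88) × 0.0378 = 0.00515.
- Var = 8.58 × 10⁻⁶ and SE = 0.00293. Then z = 0.0084/0.00293 = 2.87 and power = Φ(2.87 − 1.96) = 81.8%.
- With the average of p(1−p) = 0.03635 instead, SE = 0.00287, z = 2.92 and power = 83.2%.

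The stated figure reproduces, with a normal reference and the variance taken as known.

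**Step 2. What between-ICU variation does the ICC imply?**

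τ = √0.00515 = 0.072, against a mean rate of about 0.04. The coefficient of variation is 0.072/0.042 = 1.71 (or 1.90 against 0.0378). On the log scale, √ln(1 + 1.71²) = 1.17 (or 1.24), so about 1.2. That is very large, so 0.3 and 0.6 were also examined as more moderate assumptions.

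**Step 3. Type I error by simulation (no effect, 5,000 runs per scenario).**

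The planning rate is the one that "was estimated to be 42.0 (event rate"). Counts were Poisson with 600 × 0.042 expected per ICU-month and log-normal ICU effects. The ICU-by-month log SD was 0 to 0.2 (0 for the 1.2 scenarios). The model was a Poisson log-link GEE on the 9 × 10 cells without covariates. All SDs are assumptions. Simulation standard error is about 0.5 points at 15%.

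Uncorrected sandwich with z, nominal 5%:

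| Time term | Between-ICU log SD | Exchangeable | Independence |
|---|---|---|---|
| Categorical or linear | 0.3–0.6 | 11.9–15.3% | 15.2–18.3% |
| None | 0.3–0.6 | 8.5–12.9% | 11.8–14.3% |
| Categorical or linear | 1.2 | 22.9–24.2% | 24.3–25.5% |
| None | 1.2 | 17.4% | 21.4% |

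A cross-check with a standard GEE routine (600 runs; SD 0.3, ICU-month SD 0.15, categorical time, exchangeable) gave 14.2%.

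Corrected sandwich with t on 7 df, with a time term:

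| Correction | Log SD 0.3–0.6, exchangeable | Log SD 0.3–0.6, independence | Log SD 1.2, either |
|---|---|---|---|
| Kauermann-Carroll | 4.1–6.8% | 6.1–7.9% | 9.5–11.2% |
| Mancl-DeRouen | 2.4–5.4% | 3.7–4.8% | 4.7–6.6% |

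A permutation test over the ICU order, run separately with 999 random orders and 2,000 trials, gave 4.4–5.4%.

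**Step 4. Power for a 20% reduction after correction (exchangeable, categorical time, 3,000 runs).**

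| Between-ICU SD / ICU-month SD | Uncorrected z | Kauermann-Carroll, t(7) | Mancl-DeRouen, t(7) |
|---|---|---|---|
| 0.3 / 0 | 87.5% | 71.0% | 61.2% |
| 0.6 / 0 | 86.4% | 70.6% | 61.5% |
| 0.3 / 0.15 | 74.3% | 55.0% | 44.6% |
| 0.6 / 0.2 | 63.8% | 43.7% | 34.2% |

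Without ICU-by-month variation, the Kauermann-Carroll correction alone costs about 16 points. The remaining fall in the last two rows comes from the assumed ICU-by-month variation, which is a separate matter.

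**The case against.** The strongest reply is that the article is silent on a correction rather than against one. The sandwich variant, degrees of freedom and working correlation are details often left to an analysis plan, and none is shown here. That stands, and it rules out one tempting reading. A reader might infer that the trial's real type I error is a fixed figure around three times nominal. The documents do not support that, because they do not commit the analysis to an uncorrected sandwich with a z reference. Time adjustment is conditional and its form is open. The between-ICU SDs are assumed.

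A reader might also take the Wald Z in the Sample size section as the rule for the primary test. That sentence describes the power calculation only. It shows how the trial was planned, not how it will be analysed.

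Model-based standard errors could be used instead. With an exchangeable structure they gave 0–5.5% in these simulations, and about 3–7% in a further run at log SD 0.4. But they depend on the working correlation being right: under independence they gave about 18–46%. The article does not commit to them.

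The reply does not remove two things. GEE on nine ICUs at 0.05 is a stated choice, and every uncorrected sandwich z scenario exceeded 5%. And an unseen plan that adds a correction would leave the published 83% resting on a different test.

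**Conclusion.** The concern holds in conditional form. Ordinary GEE applied to nine ICUs as described gives an anti-conservative primary test, and the article recognises few clusters only as a balance issue. If the uncorrected sandwich z test is used, type I error is about 12–18% in the central time-adjusted scenarios (log SD 0.3–0.6), about 9–14% with no time term, and up to about 25% at the variation roughly implied by the ICC of 0.12. The direction is the same in every scenario. The size depends on between-ICU variation, time adjustment and working correlation, none of which the article fixes. The stated power is reproducible but belongs to a normal-reference test.

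**What to change.** In Statistical analysis, state that the primary p-value and confidence interval come from a small-sample-corrected GEE. One example is a Kauermann-Carroll or Mancl-DeRouen sandwich with exchangeable working correlation and a t reference on clusters minus 2 = 9 − 2 = 7 df. Support it with a randomisation test that re-draws the ICU order, which the Study design section says is randomised. Two points bear on the choice. Mancl-DeRouen tends to be conservative at moderate between-ICU variation and costs more power. Kauermann-Carroll stays near 5% there but drifts to about 10% at log SD 1.2, where the randomisation test is the more useful check.

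In Sample size, restate the power under the chosen test, with the assumed between-ICU and ICU-by-month variation given.

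The cost is wording and analysis code, with no change to the design or data collection. Intervals widen: the t multiplier alone is 2.365 against 1.960, about 21% more, before the larger standard error. The stated power will be lower than 83%.
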